## **4.4 Data Collection and Follow-Up of the Early Withdrawing Subjects**

All cases of subject withdrawal from the study will be documented.

The Investigator is responsible for recording the reasons for any premature discontinuation of the study by a patient, as well as for entering all material details into CFR, with compulsory statement of the reason for dropout.

If the patient's withdrawal was caused by AE/SAE, the Investigator should make every effort to collect the information about the outcome and record the findings into the adverse event section of the CRF. If the dropout was caused by SAE, the Investigator should follow the SAE Fast Track procedure to inform the Sponsor .

In the case of early withdrawal of the patient from the study for the reasons described in Section 4.3.1, the procedures shall be performed in accordance with the Protocol (APPENDIX 1. Study Procedure Schedule).

### **4.4.1 Replacement of Withdrawn Subjects**

In case of a dropout of a patient who was included on the basis of screening results, but who discontinued the study prior to the first administration of the study/reference product, a new patient shall be additionally enrolled instead of the excluded. The subjects who prematurely discontinue the study after they started the administration of the study/reference product will not be replaced by new patients, and their data will be taken into account (Section 15.1) in the final analysis. Laboratory tests with erroneous results during Screening may be repeated with the agreement of the Sponsor or his representative. Patients who do not meet the study inclusion/exclusion criteria due to some controlled conditions may be re-screened in consultation with the Sponsor or its representative.

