#### 3.2 Study Methodology

This study is open-label, prospective, multicenter, randomized, comparative, and parallel-arm.

According to the Screening results, , the patients who meet the inclusion criteria and are without the exclusion criteria will be randomized 1:1 to one of the treatment groups.

**Group I** is an active treatment group (50 patients), administered the medicinal product Tigerase (GENERIUM JSC, Russia) at a dose of 2.5 mg, once a day by inhalation for 24 weeks  $\pm$  1 week.

**Group II** is a reference group (50 patients), administered the medicinal product Pulmozyme® (F. Hoffmann-La Roche Ltd., Switzerland) at a dose of 2.5 mg, once a day by inhalation for 24 weeks  $\pm$  1 week.

An additional study of DNase sputum concentrations will include 24 patients from among the randomized patients (12 patients in Group I treated with Tigerase and 12 patients in Group II treated with Pulmozyme®). The DNase sputum concentration will be assessed once before the first inhalation and twice after the first inhalation of the study/reference product.

During the treatment, patients will be advised to continue the combined therapy that they received before enrollment to the study, including kinesiotherapy.

All patients enrolled in the study undergo the following successive **study periods**:

- **Screening/enrollment in the study** — for 21 days before the first administration of the study/reference product (3 weeks, Days from -21 to -1).
- **Randomization (Day 1)** — confirmed inclusion/exclusion criteria and patient allocation to one of 2 groups of therapy with a unique randomization number.
- **Therapy** — administration of the study/reference product for  $24 \pm 1$  weeks.

The duration of participation of each patient in the study, including the Screening period, will be about 28 weeks.

Upon the study completion, a final report containing the data on all patients enrolled in the study will be submitted to the regulatory authority in due course.

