#### **3.2.1.1 Randomization Procedure**

Signing the Informed Consent Form at the Screening stage, the patients are assigned a screening number. Conducting all scheduled procedures and meeting the inclusion criteria, the patient will be randomized to one of the treatment groups using the Automated Interactive System (AIS).

The stratified randomization is being used in this study. Depending on the FEV1 baseline, the patient will be allocated to one of two strata: patients with FEV 40–60% of the proper value and patients with the baseline FEV1 >60% to 100% of the proper value.

Within the two strata, the subjects will be allocated to one of two therapeutic groups at a ratio of 1:1. A unique randomization number will be assigned to each patient. Herewith, there will be no limitation of the stratum size.

Thus, the study is planned with two groups:

**Group I** is an active treatment group (50 patients), treated with investigational product Tigerase.

**Group II** is a reference group (50 patients), treated with Pulmozyme®.

The assessment of FEV1baseline will be performed at the Screening Visit. The randomization procedure and assignment of the randomization number to the patient will be performed at Visit 2 (Day 1) immediately before the study/reference product inhalation.

The registry of screened and randomized patients is maintained at all study centers. The Registration form may be found in the Study Center File. The Investigator shall regularly fill out the form entering necessary data.

In the case of early discontinuation (withdrawal from the study for any reason) of a patient, his/her randomization number shall not be reused. Newly enrolled patients will be assigned new screening and randomization numbers.

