#### **3.2.1.2 Blinding Procedure**

This study is open label. Investigators and patients will know which therapeutic regimen is being applied. The blinding procedure will be applied to the quality assessment of spirometry results at the Screening Visit, which will be assessed centrally by a certified functional diagnostics specialist who has no access to the patient's personal data, medical history, or clinical manifestations.

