#### After patient randomization

- Sputum sampling (*to study pharmacokinetics of the study/reference product in patients who signed the consent form to take part in the additional part of the study*)
- Handing over the patient diary
- Product dispensing (according to the randomization)

Inhalation of the study/reference product within the study period, including Day 1, should be performed by a patient at home using a jet nebulizer, except for patients who signed the consent form to take part in the additional part of the study to assess DNase concentration in the sputum to evaluate the pharmacokinetics of the medicinal product. These patients will receive an inhalation of the study/reference product at Visit 2 (Day 1) at the hospital using an individual nebulizer.

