## **15.2 Subset Calculation**

Within this phase II/III study, the Forced Expiratory Volume in 1 second ( $FEV_1$ ) at Week  $24 \pm 1$  week versus baseline was used as the primary efficacy endpoint. The efficacy of the investigational product Tigerase (GENERIUM JSC, Russia) will be compared with the efficacy of Pulmozyme® (F. Hoffmann-La Roche Ltd., Switzerland) in treatment of CF patients. However, since this disease is very rare, the number of patients available in Russia does not allow conducting a study using a generally accepted format of non-inferiority testing. In this regard, it is planned that the study will include all available patients aged 18 and older with an established diagnosis of cystic

fibrosis according to the relevant registries. According to preliminary information, up to 125 such patients can be available.

In this study, it is proposed to test the null hypothesis about the equality of efficacy of the two products,  $H_0: \Delta FEV_1$  (Tigerase) =  $\Delta FEV_1$  (Pulmozyme®), where  $\Delta FEV_1$  represents the change in Forced Expiratory Volume in 1 second (absolute %) on Week 24  $\pm$  1 week compared to baseline in the Tigerase and Pulmozyme® groups, respectively.

The alternative hypothesis is two-sided,  $H_a: \Delta FEV_1$  (Tigerase)  $\neq$   $\Delta FEV_1$  (Pulmozyme®). The null hypothesis will be tested using a two-tailed test at a significance level of 0.05 ( $Z_\alpha = 1.96$ ). The planned study power will be 80% ( $Z_\beta = 0.84$ ), which will allow detecting a difference ( $\delta$ ) of 5% or more between the compared groups for  $\Delta FEV_1$ , with the expected standard deviation of 10% for this parameter ( $\sigma$ ) (Table 3):

$$\delta^2 = \sqrt{\frac{4(Z_\alpha + Z_\beta)^2 \sigma^2}{n}}$$

**Table 3. Expected magnitude of differences for the primary efficacy endpoint ( $\Delta FEV_1$ ), which can be detected with the specified subset size**

| n | <math>\sigma</math> (%) | <math>\alpha</math>; 1-<math>\beta</math> (%) | <math>\delta</math> (%) |
|----------|--------------------------------|------------------------------------------------------|--------------------------------|
| 70       | 10                             | 0.05; 80                                             | 6.7                            |
| 80       | 10                             | 0.05; 80                                             | 6.3                            |

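### Replacement is tied to the first dose instead of randomization, so patients who leave after learning their open-label arm can be replaced and drop out of the primary comparison

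*Protocol*

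**What the plan says.** Protocol 4.4.1 (Replacement of Withdrawn Subjects) sets the cut-off at dosing. For a patient who passed screening but "discontinued the study prior to the first administration of the study/reference product, a new patient shall be additionally enrolled instead of the excluded". Patients who leave after starting "will not be replaced by new patients, and their data will be taken into account (Section 15.1) in the final analysis".

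Section 3.2.1.1 says that the randomization number of a withdrawn patient is not used again, and adds: "Newly enrolled patients will be assigned new screening and randomization numbers". Allocation is 1:1 within two FEV1 strata. The same section places randomization at Visit 2, directly ahead of the inhalation.

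Section 3.2.1.2: "Investigators and patients will know which therapeutic regimen is being applied".

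Section 9.1, under the steps after randomization: "Inhalation of the study/reference product within the study period, including Day 1, should be performed by a patient at home using a jet nebulizer". The exception is the sputum part, which Section 3.2 describes: "An additional study of DNase sputum concentrations will include 24 patients from among the randomized patients".

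Section 15.1 defines the safety set as patients with at least one dose, uses the same set for the primary efficacy parameters, and assigns patients to groups by intention to treat.

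On numbers, Section 1.7 plans 125 screened, 20% excluded at screening and 100 randomized. Section 15.2 intends to include all available patients: "According to preliminary information, up to 125 such patients can be available".

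**The concern.** Replacing a patient who leaves before randomization does no harm, because no allocation exists yet. After randomization in an open-label trial, the decision to leave can depend on the arm. Section 4.4.1 treats both cases alike.

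The interval is real for most patients, who go home from Visit 2 knowing their product and not yet dosed. Some enter on Pulmozyme from standard medical service (Sections 8.2 and 9.1), so one arm may continue a familiar product while the other changes. A patient who withdraws in that interval is replaced, and Section 15.1 then leaves that patient out of the primary efficacy set. What is compared is the patients willing to start what they were given, not the groups as randomized. The intention-to-treat label conceals this from a reader.

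The replacement rule is also mandatory, while the planned numbers leave no patients from whom to draw replacements.

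**Working it through.** **1. Who has an interval between known arm and first dose.** Randomized: 100 (Section 1.7). Dosed in hospital on Day 1: 24 (Sections 3.2 and 9.1). First dose at home: 100 − 24 = 76.

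**2. The plan's screening figure.** 100 / (1 − 0.20) = 125. This reproduces Section 1.7 and equals the upper end of the pool in Section 15.2, so the reserve is 125 − 125 = 0.

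**3. Screening needed with r replacements.** Formula: (100 + r) / 0.80, rounded up. The protocol gives no r, so the values are assumptions. The last column is the highest screen-failure rate at which 125 still suffices, 1 − (100 + r)/125.

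| r | (100 + r)/0.80 | Screened needed | Highest screen failure that fits |
|---|---|---|---|
| 0 | 125 | 125 | 20% |
| 1 | 126.25 | 127 | 19.2% |
| 3 | 128.75 | 129 | 17.6% |
| 5 | 131.25 | 132 | 16% |

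**4. What replacement does to arm sizes.** A replacement gets a new number and is randomized afresh 1:1. Suppose all r non-starters come from one arm and all replacements start. The expected treated numbers are then 50 − r + r/2 and 50 + r/2. For r = 5 this gives 47.5 and 52.5. The total is restored to 100, but the depleted arm is not.

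**5. Possible shift in an arm mean.** Suppose r of 50 randomized patients in one arm never start, and their mean FEV1 change would differ from the starters' mean by D. The starters' mean then differs from the mean of all 50 by (r/50) × D. Both r and D are assumptions.

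| r | D = 5 | D = 10 |
|---|---|---|
| 1 | 0.1 | 0.2 |
| 2 | 0.2 | 0.4 |
| 5 | 0.5 | 1.0 |
| 10 | 1.0 | 2.0 |

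**6. Yardstick.** Section 15.2 with σ = 10 and 1.96 + 0.84 = 2.80 gives a detectable difference of 2 × 2.80 × 10/√n = 56/√n. For n = 70, 80, 90 and 100 this is 6.69, 6.26, 5.90 and 5.60, which reproduces Table 3 (6.7, 6.3, 5.9, 5.6). I use Table 3's 5.6 at n = 100; the 5% in the text of Section 15.2 is a separate matter.

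**7. Cost of not replacing randomized patients.** If 2 to 5 randomized patients yield no data: 56/√98 = 5.66 and 56/√95 = 5.75, so about 5.7 instead of 5.6.

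**The case against.** The strongest reply is that replacement is not what removes anyone from the analysis. The at-least-one-dose set in Section 15.1 does that, and would do so with Section 4.4.1 deleted. This stands: the analysis set is the main mechanism, and the replacement rule adds to it by letting someone else fill the place. Both sections therefore need the change.

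The Protocol Summary reports that the safety population turned out identical to the full analysis set, which suggests few or no non-starters. It can also be read as basing efficacy on all included patients. Both points count against a large effect. However, Section 15.1 names the dosed set explicitly, and the two populations would also coincide if replaced patients had not been counted as included.

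Four stronger readings are tempting, and the documents do not support them:

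- A reader might infer that each arm is topped up with willing patients. Section 3.2.1.1 gives replacements new randomization numbers, so only the total is restored.
- A reader might infer that the patient pool is exceeded. That needs at least one replacement and screen failure close to the planned 20%; both the pool and the rate are approximate. The protocol shows only that there is no reserve.
- A reader might infer that refusals are hidden and the patients lost. Section 4.4 requires every withdrawal and its reason to be documented, and refers early withdrawals to Appendix 1, whose early termination visit includes spirometry. What is not provided is a Week 24 measurement for someone who never started, or a stated count of such patients by arm.
- A reader might infer that refusal is more frequent in the biosimilar arm. It is plausible, but no rate is given, and all patients consented to either product.

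**Conclusion.** The point holds as a weakness in the rule, not as a demonstrated bias. Followed as written, Sections 4.4.1 and 15.1 together allow a patient to leave because of a known allocation, be replaced, and be absent from the primary comparison. The comparison is then conditional on starting the allocated product.

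Size and direction cannot be derived from the protocol. With 1 to 5 non-starters in one arm and an assumed difference of 5 to 10 points, the shift is 0.1 to 1.0 point, probably modest against the detectable 5.6. With no non-starters it is zero. The case for change rests on keeping the randomized comparison intact at very little cost.

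The lack of reserve follows directly from the protocol's own figures: 125 screened at 20% failure gives exactly 100.

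**What to change.** - **Section 4.4.1:** allow replacement only for patients who leave before a randomization number is assigned. Every randomized patient counts toward the 100.
- **Section 15.1:** analyse the primary endpoint in all randomized patients in their allocated arm, dosed or not. Keep the at-least-one-dose definition for safety, and bring the Protocol Summary into line.
- **Follow-up and reporting:** invite randomized non-starters to the Week 24 spirometry, and report by arm how many were randomized but not treated.
- **Sections 3.2.1.1 and 9.1:** reconcile the statement that randomization directly precedes inhalation with the instruction that most patients take the Day 1 dose at home.

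The cost is a few edited sentences, some effort to obtain Week 24 spirometry from patients who never started, and possibly a few fewer treated patients. If 2 to 5 randomized patients contribute no data, the detectable difference is about 5.7 instead of 5.6. The change also removes the need to find replacements for randomized patients in a pool that has no reserve.

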## 5 INFORMATION ON THE STUDY/REFERENCE PRODUCT

### 5.1 Pharmaceutical Dosage Form, Composition, and Clinical Pharmacology of the Investigational Product

**Trade name:** Tigerase

**International nonproprietary name (INN):** Dornase alfa

**Pharmaceutical dosage form:** Solution for inhalation

**Manufacturer:** Generium JSC, Russia

**Pharmacotherapeutic group:** Expectorant mucolytic agent

**ATC code:** R05CB13

**Composition:**

|                                                |                  |
|------------------------------------------------|------------------|
| 1 mL of the medicinal product contains: |                  |
| Dornase alfa                                   | 1.0 mg (1,000 U) |
| Sodium chloride                                | 8.77 mg          |
| Calcium chloride dihydrate                     | 0.15 mg          |
| Water for injection                            | q.s. to 1.0 mL   |

**Appearance:** clear colorless or yellowish solution

**Packaging and labeling:** polymeric ampoules, 8 ampoules in a heat-sealed aluminum foil tape bag placed in a carton. The package has the following text printed with easily readable font in Russian: name of the medicinal product, information on the manufacturer, batch number, manufacturing date, shelf life, strength, volume, potency in units of activity, labeling: "For clinical studies".

**Storage conditions:** in a dark place at 2°C to 8°C.

### 5.2 Pharmaceutical Dosage Form, Composition, and Clinical Pharmacology of the Reference Product

**Trade name:** Pulmozyme®

**International nonproprietary name (INN):** Dornase alfa

**Pharmaceutical dosage form:** Inhalation solution

**Pharmacotherapeutic group:** Expectorant mucolytic agent

**ATC code:** R05CB13

**Composition:**

|                                                |                  |
|------------------------------------------------|------------------|
| 1 mL of the medicinal product contains: |                  |
| Dornase alfa                                   | 1.0 mg (1,000 U) |
| Sodium chloride                                | 8.77 mg          |
| Calcium chloride dihydrate                     | 0.15 mg          |
| Water for injection                            | q.s. to 1.0 mL   |

**Appearance:** clear colorless or yellowish solution

**Packaging and labeling:** polymeric ampoules, 6 ampoules in an aluminum foil container placed in a carton. The package has the following text printed with easily readable font in Russian: name of the medicinal product, information on the manufacturer, batch number, manufacturing date, shelf life, strength, volume, potency in units of activity, labeling: "For clinical studies".

**Storage conditions:** in a dark place at 2°C to 8°C.

### **5.3 Storage Conditions of the Study/Reference Product**

The Investigator or its authorized representative is responsible for the safe and compliant storage of the study/reference product at the study center.

The study/reference product should be retained in the study center at a temperature between 2°C to 8°C, protected from sunlight in a restricted area.

All used ampoules of the study/reference product should be stored at room temperature.

### **5.4 Accountability of the Study/Reference Product**

The Sponsor will provide the study center with the required number of the study/reference products to conduct the study. The relevant quality certificates for the study/reference product will be enclosed in the Investigator's file.

The study/reference product will be given to patients for self-inhaled daily inhalations at a dose of 2.5 mg a day at home using the jet nebulizer/compressor. The used ampoules will be collected for medicinal product registration.

Each stage of receipt, labeling, distribution, and transfer of the study/reference product will be performed and documented in accordance with the applicable clinical trial guidelines and Sponsor's standard operating procedures.

The responsibility for medicinal product registration in the study center rests with the Principal Investigator, who may delegate some of the authority for medicinal product registration to the appropriate employee.

The Investigator should ensure that the study/reference product is used in strict compliance with the protocol instructions.

The study/reference product registration should be maintained by the Principal Investigator or his/her designated Responsible Investigator on specific forms for the recording, storage, and distribution of medicinal products in accordance with the pharmaceutical trial guidelines. The Investigator should keep records of the receipt of the medicinal product, storage conditions, and all procedures with the investigational product at the study center in the Investigator's file.

The study/reference products retained by the Investigator should be stored in closed areas with limited access. The Investigator must keep all used, unused, or partially used packages of the medicinal product until directed by the Sponsor.

## **5.5 Dosing Schedule of the Study/Reference Product**

The investigational product Tigerase/reference product Pulmozyme® is inhaled at a dose of 2.5 mg (which corresponds with the contents of 1 ampoule — 2.5 mL of undiluted solution, 2,500 U) once daily, at the same time without dilutions, using the jet nebulizer/compressor.

The study/reference products are used as a part of combined therapy including chest physical therapy.

The first inhalation of the study/reference product is on the Randomization Day – Day 1.

## **5.6 Preparation of the Study/Reference Product for Use**

*Administration of the investigational product Tigerase/reference product Pulmozyme® using the jet nebulizer:*

The study/reference product solution in the ampoules intended for single inhalation only should not be diluted or mixed with other medicinal products or solutions in the jet nebulizer cup. Mixing the product with other medicinal products can lead to undesirable structural and/or functional changes in Tigerase/Pulmozyme or another mixture component.

The contents of one ampoule are poured into the jet nebulizer cup equipped with a mouthpiece and a mask. The jet nebulizer is connected to the compressor to create the required airflow (5–8 L/min); a fill volume of the jet nebulizer should be 2–4 mL.

Since dornase alfa applied as a solution through the jet nebulizer enters the lungs during inhaling, the medicinal product should be inhaled through the mouthpiece calmly and evenly. Patients who have difficulties breathing through the mouth during the entire inhalation period using the jet nebulizer may use the jet nebulizer equipped with a tight-fitting mask.

**Attention!** Ultrasonic nebulizers are not suitable for the administration of the study/reference product as they may inactivate dornase alfa or fail to provide the required aerosol characteristics.

*Inhalation procedure:*

1. Before performing the procedures described below, wash hands thoroughly.
2. Assemble the jet nebulizer and attach the mouthpiece or respirator according to the manufacturer's instruction.
3. Open the ampoule of the study/reference product and pour the contents into a special jet nebulizer cup.
4. Place the mouthpiece between your teeth and close your lips tightly around it (when using a respiratory mask, put it on so that it fits tightly on the face).
5. Switch on the compressor.
6. Start breathing deeply and slowly, holding your breath for 2 seconds after inhaling, exhale through the nose (rapid deep breathing may cause dizziness, so interrupt the inhalation for a short time from time to time).
7. The inhalation of the study/reference product continues until the medicinal product is used (prior to intermittent aerosol delivery).
8. Switch off the compressor.
9. Rinse your mouth with boiled water (when using the respiratory mask, rinse your eyes and face with water).
10. Dismantle the jet nebulizer.
11. Wash and dry the system components in accordance with the manufacturer's instruction.

*Warning:*

- Inhalations are carried out not earlier than 1–1.5 hours after eating or physical activity.
- Keep calm during inhalation; make sure that clothes do not hug your neck or make breathing difficult.
- Before inhalation, there is no need to take expectorants or rinse the mouth with antiseptic solutions (potassium permanganate, hydrogen peroxide, boric acid).

The patients will be advised to follow the manufacturer's instructions for the operation and maintenance of the jet nebulizer/compressor.

